#### **8.5.3 12-Lead ECGs**

12-Lead ECGs will be recorded after 5 minutes supine rest on the Day of screening visit, Day 0, Day 14±1, Day 28 and at follow up (See Appendix B). The 12-lead ECGs will be recorded in triplicate at each time point, with each ECG separated by approximately 1 minute at each time point.

#### **8.5.4 Physical examinations**

A full physical examination will be performed on the day of screening visit. Abbreviated Physical examination will be done on Day 0, Day 28 and Follow-up.

#### **8.5.5 Chest X ray**

Chest X ray will be performed only in India and on the day of screening to exclude pulmonary TB-infection.

#### **8.5.6 Laboratory investigations and bioanalysis of blood samples**

The sampling schedule for laboratory assessments are as mentioned in Appendix B. The Safety laboratory investigations will be done at the local lab of the respective study centre. The analysis of metabolic biomarkers (mentioned in Appendix A and B), endocrinology assessments of all 40 Subjects will be done at Academic Medical Centre, The Netherlands. Also, bioanalysis of blood samples for the determination of

---

glucose and glycerol enrichment of all 40 Subjects will be done at Advanced Laboratory of Endocrinology, AMC, [name], [name]. Blood samples collected from Study subjects at Veeda Clinical Research Ahmedabad for evaluation of the parameters mentioned above will be sent to AMC, The Netherlands.

#### *Blood sampling*

Blood sampling will be done for glucose monitoring (for maintaining Euglycemia) at every 10 minutes. A window of  $\pm 1$  minute will be allowed. Blood samples will be taken at the following time points relative to the start of continuous glucose infusion (taken as  $t=0$ ): T= -2:00, -0:05, -0:00, 0:05, 1:50, 1:55, 2:00, 2:05, 2:10, 4:00, 4:05, 4:10, 4:15, 4:20 (14 samples during one clamp procedure).

The actual time of blood sampling will be recorded in the CRF. At each time point, the blood samples will be collected into the appropriate polypropylene tube. The tubes will be inverted gently 8 to 10 times before processing. The tubes will be kept in an ice bath before centrifugation. Within 30 minutes of blood sample collection, the samples will be centrifuged at approximately 3000 g for 10 minutes at 4°C. The plasma obtained from each sample will then be transferred into four labeled polypropylene tubes and frozen immediately. The tubes will be stored at a temperature below -70°C prior to shipment. One set of samples will be sent to the Advanced Laboratory of Endocrinology, AMC the Netherlands for bioanalysis of each  $d_2$ -glucose and  $d_5$ -glycerol, insulin, cortisol, glucagon, catecholamines, other biomarkers and as duplicate and back-up. All safety laboratory investigations will be done at the local lab of the respective study centre.

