arm. One catheter is used for sampling of arterialised blood using a heated hand box (60°C). The other catheter is used for infusion of [6,6-2H2]-glucose en and [1,1,2,3,3-2H2]-glycerol, glucose 20% and insulin. At t= -2hr, after drawing a blood sample for background enrichment of plasma glucose, a continuous infusion of [6,6-2H2]-glucose (>99% enriched, Cambridge Isotopes, Massachusetts, USA) is started at a rate of 0.11 µmol/kg per min after a priming dose equivalent to 100 min of infusion. After 1 hr, a continuous infusion of [1,1,2,3,3-2H2]-glycerol (>99% enriched, Cambridge Isotopes, Massachusetts, USA) is started at a rate of 0.11 µmol/kg per min after a priming dose of 1.6 µmol/kg/min. The first 2 infusion hrs are required for equilibration. After 115, 120 and 125 min blood samples are drawn for determination of glucose and glycerol enrichment to calculate basal endogenous glucose production and lipolysis, glucoregulatory hormones and FFA. Subsequently, the hyperinsulinemic clamp will start with a continuous infusion of insulin (Actrapid 100U/ml, Novo Nordisk ) for 2hr at a rate of 20mU/m^2 body surface area per min. Plasma glucose is measured every 10 min (Biosen C-line plus glucose analyzer; EKF Diagnostics, Barleben/Magdeburg, Germany at AMC, Netherlands; and YSI analyzer at Veeda Clinical Research India) and glucose 20% is infused at a variable rate to maintain plasma glucose at 5.0 mmol/l or 90 mg/dl. [6,6-2H2]-glucose is added to the 20% glucose solution to achieve glucose enrichments of 1% to minimize changes in isotopic enrichment due to changes in the infusion rate of exogenous glucose, and thus to allow for accurate quantification of endogenous glucose production and uptake. During the last 20 min of the hyperinsulinemic clamp, blood samples are drawn at 5 min intervals for determination of glucose and glycerol enrichment, glucoregulatory hormones and FFA. At t= 2.15hr, the infusion of insulin is increased to a rate of 60mU/m^2 body surface area per min. Plasma glucose is measured again every 10 min and enriched glucose 20% is infused at a variable rate to maintain plasma glucose at 5.0 mmol/l or 90 mg/dl. During the last 20 min of this insulin infusion step, blood samples are drawn at 5 min intervals for determination of glucose and glycerol enrichment, glucoregulatory hormones and FFA. Thereafter insulin infusion will be discontinued and participants will be offered a carbohydrate rich meal. The glucose infusion rate will be doubled. Plasma glucose levels will be measured every 10 minutes for the first hour. Thereafter blood glucose measurement will be done at 20 minute intervals or more frequently (at the discretion of the

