| 11:00                                               | 0 and 28  | 0:00             |                                                                                                                                                                                                                                                                                                                                                                                                                                                                                                                                                                                                                                                                                                                                               |
| 11:00                                               | 0 and 28  | 0:00             | The hyperinsulinemic clamp will start with a continuous infusion of insulin (Actrapid 100U/ml, Novo Nordisk) for 2h at a rate of 20mU/m  body surface area per min.                                                                                                                                                                                                                                                                                                                                                                                                                                                                                                                                                               |
| 11:00-13:05
BG will be estimated at every 10 min | 0 and 28  | 0:00-2:05        | Plasma glucose is measured every 10 min (via Biosen/YSI analyzer) and glucose 20% is infused at a variable rate to maintain plasma glucose at 5.0 mmol/l. [6,6-2H 2 ]-glucose is added to the 20% glucose solution to achieve glucose enrichments of 1% to minimize changes in isotopic enrichment due to changes in the infusion rate of exogenous glucose, and thus to allow for accurate quantification of endogenous glucose production and uptake                                                                                                                                                                                                                                                                             |

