| 15:05                                              |          | 4:05 |                                                                                                                                                                                                                                                                                                                                                |
| 15:10                                              |          | 4:10 |                                                                                                                                                                                                                                                                                                                                                |
| 15:15                                              |          | 4:15 |                                                                                                                                                                                                                                                                                                                                                |
| 15:20                                              |          | 4:20 |                                                                                                                                                                                                                                                                                                                                                |
| 15:20                                              | 0 and 28 | 4:20 | Stop insulin infusion & Double the glucose infusion rate                                                                                                                                                                                                                                                                                       |
| 15:20                                              | 0 and 28 | 4:20 | Provide a carbohydrate rich meal to volunteer.                                                                                                                                                                                                                                                                                                 |

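### The clamp timetable contradicts itself: combining the Appendix B sampling times with the Appendix C insulin start puts one of three basal samples 5 minutes after insulin begins.

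*Protocol*

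**What the plan says.** Four places in the protocol time the clamp.

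- **Section 8.4.1** starts the tracer two hours before zero: "At t= -2hr, after drawing a blood sample for background enrichment of plasma glucose, a continuous infusion of" labelled glucose. It then fixes the basal samples: "After 115, 120 and 125 min blood samples are drawn for determination of glucose and glycerol enrichment to calculate basal endogenous glucose production and lipolysis". Insulin follows these samples, with no clock time given. The first step is to last 2 hours, and the rate is raised at 2:15.
- **Section 8.5.6 (Blood sampling)** gives the list "T= -2:00, -0:05, -0:00, 0:05, 1:50, 1:55, 2:00, 2:05, 2:10", completed by "4:00, 4:05, 4:10, 4:15, 4:20 (14 samples during one clamp procedure". It counts these times "relative to the start of continuous glucose infusion". The same section names Appendix B as the sampling schedule.
- **Appendix B** labels the basal columns both as 115, 120 and 125 min and as -0:05, 0:00 and 0:05.
- **Appendix C** lists basal samples at -0:10, -0:05 and 0:00. Its row for T = 0:00 reads "The hyperinsulinemic clamp will start with a continuous infusion of insulin (Actrapid 100U/ml, Novo Nordisk) for 2h". It gives the first-step glucose window as 0:00 to 2:05, the first-step samples as 1:50 to 2:10, and the second insulin step as 2:15 to 4:15. At T = 4:20 it takes the last sample and instructs "Stop insulin infusion & Double the glucose infusion rate".

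The synopsis (Methodology) sends the reader to Appendix C for the clamp procedure. The visit lists in section 8.5 send the reader to section 8.4.1.

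**The concern.** Suppression of endogenous glucose production and suppression of lipolysis are two of the three insulin-sensitivity criteria in the synopsis, and hepatic insulin sensitivity is part of the main endpoint in section 8.1.1. Both are judged against the basal value, which section 8.4.1 takes from these three samples. If one of them is drawn after insulin has started, it is no longer a basal measurement. To the extent that insulin has begun to act, the basal value is too low and suppression is understated.

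Two centres run the clamp separately, 20 subjects each, and a secondary objective compares ethnic groups. If the centres work from different tables, a timing difference between them adds to a comparison in which centre and ethnicity already largely coincide. The clamp is done only twice per subject, so a mistimed sample cannot be recovered later.

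**Working it through.** No sample-size or power figure enters this point; the check is clock arithmetic.

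**1. The plan's own count.** Section 8.5.6 lists 1 background + 3 basal + 5 first-step + 5 second-step samples = 14, as stated.

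**2. The four places side by side.**

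| Item | Section 8.4.1 | Section 8.5.6 and Appendix B | Appendix C |
|---|---|---|---|
| Basal samples | 115, 120, 125 min | -0:05, 0:00, 0:05 | -0:10, -0:05, 0:00 |
| Insulin start | after the basal samples, no clock time | not given | 0:00 |
| Step 1 length | 2 h | not given | 2 h; glucose window to 2:05 |
| Step 1 samples | last 20 min | 1:50 to 2:10 | 1:50 to 2:10 |
| Rate increase | 2:15 | not given | 2:15 |
| Step 2 window | no end time | not given | 2:15 to 4:15 |
| Step 2 samples | last 20 min | 4:00 to 4:20 | 4:00 to 4:20 |
| Insulin stop | after sampling | not given | 4:20 |

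**3. Basal samples in minutes from the tracer start at -2:00 (add 120).**
- Section 8.5.6 and Appendix B: -5, 0, +5 become 115, 120, 125. These match section 8.4.1.
- Appendix C: -10, -5, 0 become 110, 115, 120. These do not.

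Three places therefore agree and Appendix C differs. Appendix C has no 0:05 sample; the other three have no -0:10 sample.

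**4. Combining the tables.** With insulin at 0:00 (Appendix C) and samples at -0:05, 0:00 and 0:05 (Appendix B), the 0:05 sample is 5 minutes after insulin start: 1 of 3. Appendix B also draws one of its three basal insulin samples then. It draws FFA, glucagon, catecholamines and cortisol only at 0:00 in the basal period, so the 0:05 time does not touch them.

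**5. Step 1, by assumed insulin start** (end = start + 120 min).

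| Insulin start | Basal samples after start | 2 h ends | Step 1 samples after that end |
|---|---|---|---|
| 0:00 | 0:05 | 2:00 | 2:05, 2:10 |
| 0:05 | none | 2:05 | 2:10 |
| 0:10 | none | 2:10 | none |
| 0:15 | none | 2:15 | none |

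From 0:00 to the rate increase at 2:15 is 135 minutes, against a stated 120.

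**6. Step 2.** Against the stated end of 4:15, the 4:20 sample is 5 minutes late. Against the stop instruction at 4:20, none is late. From 2:15 to 4:20 is 125 minutes. Appendix C's tracer durations fit 4:20: from -2:00 to 4:20 is 6:20 h (glucose), and from -1:00, the glycerol start in section 8.4.1, to 4:20 is 5:20 h.

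**7. Zero point.** The infusion of labelled glucose that section 8.4.1 calls continuous begins at -2:00, so t=0 cannot be its start. If section 8.5.6 means the variable 20% glucose, t=0 falls at insulin start on the Appendix C timetable and the 0:05 conflict remains.

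**8. Size.** Suppose the three values are averaged with equal weight (an assumption) and the post-insulin value is a fraction x below basal. The mean is then (1 + 1 + (1 - x))/3 = 1 - x/3. The documents give no value for x, so the calculation stops there.

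**The case against.** Each description of the basal period is coherent alone. Section 8.4.1 draws all three samples and then starts insulin. Appendix C starts insulin at 0:00 but has no sample after that until 1:50. A reader might infer that Appendix C itself schedules a post-insulin basal sample; it does not. The problem needs a site to combine two tables. This stands as a limit on the point, but the protocol's own cross-references invite the combination.

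A reader might also infer that the 2:05, 2:10 and 4:20 samples are taken with the step's infusion off. The documents do not show this. Nothing tells a site to stop or change insulin between 2:00 and 2:15, an increase at 2:15 implies that the first rate is still running, and the explicit stop is at 4:20. What remains is that the stated step lengths and glucose windows disagree with the sampling, change and stop times.

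The treatment comparison is largely protected. Allocation is 1:1 within each site and the second clamp is to use the same method, so a consistent site error falls on both arms and both visits. Glucose disposal, the only variable in the sample-size statement, is measured under insulin and does not use the basal mean. Centre and ethnicity are largely inseparable by design anyway, and nothing shows that the centres would follow different tables.

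Finally, a rule on which samples enter a mean could sit in an analysis plan that is not shown. That is fair for the rule, but an analysis plan cannot remove conflicting timings from the procedure that sites carry out.

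**Conclusion.** The inconsistency is real and should be corrected. Basal sample times and insulin start differ between Appendix C and the other three places. Following the cross-references as written can put 1 of 3 basal samples 5 minutes into the insulin infusion. Separately, the stated step lengths do not match the sampling, rate-change and stop times, and the zero of the clock conflicts with the tracer start.

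The conclusion rests on one condition: that a site samples by Appendix B and infuses by Appendix C. The bias would be one third of whatever fall has occurred in that sample, under equal weighting. A reader might insert an assumed fall and quote a distorted suppression percentage, but no such figure has support in the documents. The exposure is to the validity of the two suppression measures and to the centre or ethnic comparison; a material bias between the randomised arms is not shown.

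**What to change.** 1. Reconcile section 8.4.1, section 8.5.6, Appendix B and Appendix C to one clock, used at both centres, with a single insulin start, step-change time and stop time. Step lengths and glucose windows should agree with it. Which timing is right is for the sponsor and investigators to settle.
2. Correct the definition of t=0 in section 8.5.6 so that it names one event.
3. Record the actual insulin start, step-change and stop times in the CRF. Section 8.5.6 already records actual sampling times, but not these.
4. State that only samples taken before the actual insulin start enter the basal mean. If a basal sample and the insulin start keep the same nominal time, as at 0:00 in Appendix C, say which comes first.

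The cost is corrected times in these places, three recorded times per clamp, and one sentence on the basal mean. No extra blood sample or visit is needed.

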#### *Shipment*

The plasma samples for bioanalysis will be shipped to the following bioanalytical facility on dry ice, with a portable data logger (sample shipment log):

Laboratory of Special Endocrinology, AMC

[name]

[name]

The samples will be checked by the bioanalytical facilities as soon as possible after they are received, and receipt will be documented.

#### 8.5.7 *Bioanalysis*

Plasma samples will be analysed using a validated GCMS method.

#### 8.5.8 *Sample retention / destruction*

The plasma samples will be retained by the bioanalytical facilities for 1 month after the final study report has been signed off. The samples will be destroyed/returned back to sponsor after obtaining written consent from the sponsor for the same. Duplicate Samples will be sent to the bioanalytical facility after the confirmation of receipt of first set is provided to the study centre.

### 8.6 Appropriateness of Measurements

All planned assessments are standard measurements for this type of study and are considered appropriate.

### 8.7 **Total Volume of Blood**

**Table 1: Summary of Blood Volumes for Each Subject**

| Requirement                                                                    | Number and Volume of Samples | Total    |
|---------------------------------------------------------------------------------------|-------------------------------------|-----------------|
| Clinical laboratory tests                                                             |                                     |                 |
| Hematology, endocrinology                                                             | 20 x 4.5 ml                         | 90              |
| Haemostasis                                                                           | 5 x 2.7 ml                          | 13.5            |
| Biochemistry                                                                          | 5 x 4.5 ml                          | 22.5            |
| Viral Serology                                                                        | 1 x 10 ml                           | 10              |
| SIRT(for subjects at Veeda CR only)                                                   | 3 x10 ml                            | 30              |
| Clamp Day (including baseline measurements, reserve samples and glucose during clamp) | 2 x (125.1ml+ 20x 0.5ml (glucose))  | 270.2           |
| Total                                                                          |                                     |                 |
| For subject at AMC                                                             |                                     | 406.2ml  |
| For subject at Veeda CR                                                        |                                     | 436.2 ml |

---

## 8.8 Withdrawal Criteria

Subjects may decide to withdraw from the study at any time without prejudice to their further medical care. Although a subject is not obliged to give his reason(s) for withdrawing prematurely from a trial, the investigator should make a reasonable effort to ascertain the reason(s) while fully respecting the subject's rights. The investigator may withdraw a subject for any of the following reasons:

- adverse event: if subject is unwilling to continue because of an AE or if continued participation of the subject would be an unnecessary risk to the subject's health, in the opinion of the investigator
- non-compliance
- protocol deviation
- lost to follow-up
- study blind is broken
- sponsor request
- following review of safety/tolerability data
- other.

## 8.9 Withdrawal Procedures

If a subject withdraws from the study, the primary reason for withdrawal must be recorded in the CRF. The procedures scheduled for early withdrawal should be performed if possible, as well as any other additional procedures requested by the investigator for safety purposes. The last date of study drug administration must be documented. Appropriate follow-up of withdrawn subjects will be performed, as required. Attempts to contact a subject who withdraws from a study must be documented.

## 8.10 Replacement of Dropout/Withdrawals

Replacement of dropout/withdrawals will be done by Pharmacy personnel at the CRU, who is unblind to the study drug. Pharmacist at the CRU will manage any dropout/withdrawal by providing different subject ID and randomisation code to the reserve subject but will receive same drug (active treatment/placebo) as allotted to the replaced subject. For example, if subject 002 is withdrawn, then the first replacement

---

will be allocated with randomisation code A002, if second replacement of same subject happen then B002, for third replacement C002.

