## **6. STUDY POPULATION AND TREATMENT**

### **6.1 Number and Description of Subjects**

It is intended that 40 subjects complete the study: 20 subjects in India and 20 subjects in Amsterdam, the Netherlands. An attempt will be made to dose 20 subjects at each study site (10 for Active treatment; 10 for Placebo treatment). Subjects will be identified by their initials. In addition, subjects will be given a screening number at screening and a subject (randomisation) number at the time of randomisation. A list identifying the subjects by initials, screening number, subject number and status (completed study/withdrawn) will be kept in the trial master file.

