#### **6.4 Sample Size Calculation**

It is intended that 40 subjects (20 subjects in India and other 20 in Amsterdam, the Netherlands) will complete the study. No formal sample size calculation has been performed. We calculated that a sample size of 20 in each group will have 80% power to detect an absolute difference in Rd of at least 15  $\mu\text{mol/kg}\cdot\text{min}$  (measure for peripheral insulin sensitivity), before and after treatment, using a Wilcoxon (Mann-Whitney) rank-sum test with a 0.05 two-sided significance level and assuming that the common standard deviation is 15.

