#### **8.2.2 *Breaking the randomisation code***

The investigator will have access to one set of sealed code-break envelopes. In the event of an emergency, e.g. a serious adverse event (SAE), the investigator may open the subject's envelope to determine the study drug administered to the subject. If

---

possible, the sponsor should be notified before the blind is broken; otherwise, the sponsor will be notified as soon as possible. In addition the IEC (Independent Ethics Committee) will also be notified if the code is broken during the study. The date, time and reason, and the name of the person who opened the envelope, will be recorded in the subject's CRF and on the individual envelope. If the blind is broken, the subject must be withdrawn from the study and replaced.

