### **8.3 Blinding**

This will be a double-blind design. The subjects and investigator (and other personnel involved in the study) will be unaware of the study drugs administered to individual subjects.

Personnel in the biometrics department at Academic Medical Centre and Veeda Clinical Research will be blind during the study, except for a nominated individual(s) responsible for preparing the randomisation code and code-break envelopes. The sponsor will remain blind during the study. The placebo tablets will be identical in appearance and taste to the TRC150094 tablets administered at the corresponding dose level, and the same number will be administered. Pharmacy personnel at the study centre who prepare and check the individual unit doses from the bulk packaging will be the only staff at the study centre that is not blind to the study drug. At regular monitoring visits, a study monitor will check the blind is maintained during dosing and during the study, and that all code-break envelopes remain intact. The monitor will remain blind during the study, and steps must be taken during monitoring such that treatment allocation is not revealed.

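### A replacement inherits the withdrawn subject's arm under a linked code, so a code break, which makes replacement compulsory, tells the investigator the replacement's treatment

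*Protocol*

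**What the plan says.** Four parts of the protocol bear on this.

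- **Section 8.10.** Pharmacy staff who know the treatment codes carry out replacements. They do so by "providing different subject ID and randomisation code to the reserve subject but will receive same drug (active treatment/placebo) as allotted to the replaced subject". As the worked example, the first replacement for subject 002 "will be allocated with randomisation code A002"; second and third replacements carry the prefixes B and C.
- **Section 8.2.2.** The investigator holds sealed envelopes and may open one in an emergency, such as a serious adverse event, to learn the treatment. The rule that follows is: "If the blind is broken, the subject must be withdrawn from the study and replaced".
- **Section 8.3.** "The subjects and investigator (and other personnel involved in the study) will be unaware of the study drugs administered to individual subjects".
- **Sections 6.1 and 6.4.** The target is counted in completers: "It is intended that 40 subjects complete the study". The planning statement is: "We calculated that a sample size of 20 in each group will have 80% power".

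**The concern.** Each rule looks workable alone, but together they conflict. A code break tells the investigator one subject's treatment and sets off a replacement whose treatment is by rule the same. The code given to the replacement points back to the opened envelope. For that replacement the study is no longer double-blind towards the investigator, and this is known before the first dose.

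Some outcomes depend on the investigator's judgement. Under Section 9.1.4 the investigator rates how each adverse event relates to study drug, and safety is half of the primary objective in Section 4.1. The clamp in Section 8.4.1 relies on staff adjusting a glucose infusion to hold a target. Knowledge of the arm could colour either, and an unblinded subject cannot be blinded again.

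There is also a departure from the allocation method. Section 8.2.1 describes 1:1 randomisation on Day 0, with consecutive numbers in order of inclusion. A reserve subject under Section 8.10 is instead placed in an arm that is already fixed and is known to the staff who place him.

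**Working it through.** **1. The plan's own figure.** Section 6.4 gives 20 per group and 80% power "to detect an absolute difference in Rd of at least 15" µmol/kg·min, "using a Wilcoxon (Mann-Whitney) rank-sum test with a 0.05 two-sided significance level", with a standard deviation of 15. Noether's formula for the Mann-Whitney test gives:

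- p = Φ(15 / (15 × √2)) = Φ(0.707) = 0.760
- N = (1.960 + 0.842)² / (12 × 0.25 × (0.760 − 0.5)²) = 38.6 in total, or 19.3 per group, rounded up to 20
- Power at 20 per group = Φ(√(3 × 40) × 0.2602 − 1.960) = 81.4%

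The stated size reproduces. It refers to 20 per group with an Rd result, which is what replacement is meant to secure. With 1, 2, 3 or 4 losses per arm and no replacement, the same formula gives 79.4%, 77.2%, 74.8% and 72.2%. Replacement therefore has a legitimate purpose, and the question is only how the replacement is allocated.

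**2. The chain after a code break.**

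- The investigator opens the envelope of 002 and learns the arm (8.2.2).
- Subject 002 must be withdrawn and replaced (8.2.2).
- The replacement gets the drug that 002 was allotted (8.10).
- The replacement is coded A002 (8.10). Section 8.2.1 makes subject number and randomisation number equivalent, and Section 12.1 uses subject ID and randomisation number to identify subjects on the eCRF, so the code is in the investigator's view.
- Hence the investigator knows the arm of A002 before dosing. Section 8.3 says the opposite.

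**3. The chain without a code break.** Subject 002 leaves for another reason, with the envelope sealed. The investigator does not know the arm of 002. The code A002 shows that the two subjects share an arm but not which arm. The blind holds.

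**4. Size.** Each code break that is followed by a replacement gives one replacement with known treatment: 1/20 = 5% of a centre's completers, 1/40 = 2.5% overall. The protocol gives no expected number of breaks. For an assumed 1, 2 or 4, the share overall is 2.5%, 5% or 10%.

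**5. Price of unlinked allocation.** If fresh randomisation leaves one centre at 11:9 instead of 10:10, the ratio of standard errors is √((1/11 + 1/9) / (2/10)) = 1.005, an increase of about 0.5%.

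**The case against.** The strongest reply is that the slot was itself randomised. The pharmacist applies a rule and has no say over which arm a given vacancy belongs to, and inheriting the arm keeps each centre at 10:10. Code breaks are reserved for emergencies, and Section 7.2.3 reports no serious adverse events in the single-dose studies, so few are likely. Nothing says that the replacement himself learns his treatment. All of this stands, and it limits the defect in extent. It does not remove the conflict between Sections 8.2.2, 8.3 and 8.10. Nor can an analysis plan repair it, because these rules act while the trial is running.

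A reader might infer more than the document supports:

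- **That the trial becomes a comparison of selected completers.** No section excludes withdrawn subjects from the efficacy analysis. Section 6.1 sets a target number, not an analysis population, and the efficacy set may be defined in an analysis plan that is not shown. Section 8.11 asks for observations to be reported up to withdrawal.
- **That withdrawn subjects drop out of the safety analysis.** Section 10.4 uses the Safety Set and takes subjects treated as the denominator.
- **That replacement biases Rd by a calculable amount.** Any such figure needs an assumed number of withdrawals and an assumed difference between those who leave and those who stay; the protocol gives neither. The loss of Rd data comes from the schedule: the clamp is done on Day 0 and Day 28, and the follow-up assessments due after withdrawal include none. That loss would occur without replacement too. If k subjects who lie D away from the arm mean leave, the mean of the rest shifts by kD/(20 − k); refilling with typical subjects gives kD/20, which is smaller.
- **That the sponsor and ethics committee also learn the arm.** Section 8.2.2 has them notified of the break and does not say that they are given the allocation.

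**Conclusion.** The point holds in a limited form. For any replacement that follows a code break, the investigator who opened the envelope knows the arm before dosing, contrary to Section 8.3. This follows from the protocol's own rules. It rests only on the investigator seeing the replacement's code, which Sections 8.2.1 and 12.1 imply. Each such break affects one subject, and the total cannot be stated because no rate is given. Separately, every replacement is assigned by unblinded staff to an inherited arm instead of being newly randomised; without a code break this does not disclose the arm to the investigator.

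The protocol should be corrected, preferably before enrolment. The defect does not by itself undermine the efficacy or safety comparison, and the stated sample size is not in error.

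**What to change.** Reconcile Sections 8.2.2, 8.3 and 8.10. In 8.10, let each replacement take the next unused number from a reserve block generated in advance on that centre's randomisation list, with no link in treatment or number to the subject replaced. Drop the A, B and C prefixes. State in 8.2.2 and 8.10 that replacements are additional to the randomised subjects and do not substitute for them, and that data already collected from withdrawn subjects are kept.

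The cost is protocol wording and a longer list with matching envelopes at each centre. Arms may end slightly unequal, at the small price in precision shown in the working. Replacement still protects the number of subjects with an Rd result, so the purpose of the present rule is preserved.
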